#### 3.1 Study period

| *Phase/year* | ***2014*** | ***2015*** | ***2016*** | ***2017*** | ***2018*** |
| --- | --- | --- | --- | --- | --- |
| Scientific project | X |  |  |  |  |
| Ethics committee submission |  | X |  |  |  |
| Data collection and follow up* |  | X** | X | X | X |
| Laboratory analysis |  |  |  | X |  |
| Data analysis |  |  |  | X | X |
| Manufacture of scientific articles |  |  |  |  | X |

* The deadline for the final analysis of data from the follow-up period will be February 2018.

* * The Collection can only be initiated after approval by the ethics committee.

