3.2 Sampling type and sample size definition

The sample will be systematic random.

It will be included sequentially patients over 18 years of age with moderate to severe plaque psoriasis with the indication of methotrexate referred by dermatologists to initiate the follow-up in the outpatient clinics of the Hospital of the Federal University of Pernambuco who meet the eligibility criteria and sign the consent form.

The sample size calculation was performed considering the effect of MTX on PASI. The calculation used the formula for comparing paired differences.

To achieve a power of 80 % and a level of significance of 5 % (two-sided) for detecting an effect size of 0,65 between pair was necessary 22 pairs.

For the other variables, the objective was to verify if this effect produced on the PASI would be sufficient to produce a change in them.

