**Follow up period**

1. The patient will be scheduled every three months to check the PASI and the laboratory results: Complete blood count, liver enzymes, renal function, CPR, ESR, and pregnancy test for women. Fast blood glycemia and cholesterol will be requested according to the need of each patient.
2. The follow-up period of the study will end in February 2018. However, the patients will be kept on follow-up at the outpatient clinic for an indeterminate period, unless they abandon follow-up.
3. In case of loss of PASI response to below 50%, patients will have their medication modified according to each case by main research.

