| Place of residence | Urbanization of the place of residence | Interview | 1. Urban zone 2. Rural area |
| Contact with cattle | A person who has worked or had contact for a long time with cattle | Interview | 1. Yes 2. No |
| Nail psoriasis | Presence of pits, onycholysis, splinter hemorrhages, and hyperkeratosis not attributed to another cause in at least one nail. | Physical exam | 1. Yes 2. No |
| Geographical language | Smooth red spots on the tongue | Physical exam | 1. Yes 2. No |
| Psoriasis Scalp | Presence of psoriasis plaques on the scalp | Physical exam | 1. Yes 2. No |
| Palmoplantar psoriasis | Presence of psoriasis plaques on the palms or plants may transgress to the back | Physical exam | 1. Yes 2. No |
| Inverted psoriasis | Presence of psoriasis plaques fold areas | Physical exam | 1. Yes 2. No |
| Enthesitis | Patient presents pain on palpation of entheses without signs of arthritis | Physical exam | 1. Yes 2. No |
| Diabetes | Use of medication for diabetes or two fasting blood glucose levels above 126 mg/dl or an aleatory blood glucose level above 200 mg/dl. | Interview Laboratory tests | 1. Yes 2. No |
| Blood glucose | in mg/ml. | Laboratory tests | average |
| Chest X-ray suggestive of LTBI | Presence of retraction, calcification, hilar or mediastinal lymph node enlargement, or pleural alterations. | Image examination | 1. Yes 2. No |

| Variable | Definition | Method | Categorization |
| --- | --- | --- | --- |
| Treatment maintenance | Defined as patients who achieved 50% or more reduction in PASI score after 12 weeks of treatment and maintained this reduction until the end of the follow-up period. | Physical exam | Sustainer |
|  | Defined as patients who did not achieve a 50% reduction in PASI or those who did but lost response over the follow-up period and need a change in medication. | Physical exam | Non-sustainer |

- 1. Collection techniques
     1. **PASI**

The PASI will be carried out according to the methodology described below:

1) Each body area (head, trunk, upper limbs and lower limbs) will have their percentage of involvement determined by the researcher and will receive a number according the percentage of committed area: 1 < 10%; 2 = 10-29%; 3 = 30-49%; 4 = 50-69%; 5 = 70-89% and 6 = 90-100%

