#### Data analysis plan

The IBM Statistical Package version 23.0 (IBM corp., Armonk, NY) will be used for the statistical calculations.

- Data will be analyzed descriptively through statistical measures: mean ± standard deviation or median and percentiles for numerical variables and absolute and percentage frequencies for categorical variables.
- It will be verified whether there is a significant change in the results of TST and/or IGRA tests, with 2 or 3 categories, classified according to the variables descriptions by the McNemar test. A P < 0,05 will be considered significant.
- It will be verified whether the difference in the comparison of test results is significant before and/ or after treatment by the McNemar test. A P < 0,05 will be considered significant.
- The agreement between each and between the IGRA and the TST before and after treatment, with two or three categories, will be verified by the Cohen’s kappa.
- For numeric continuous variables, the normality will be tested using the Shapiro-Wilk test. To compare the mean of paired continuous variables will be used the Student's t-test for paired variables for variables with a normal distribution, and the Wilcoxon test for variables with a non-normal distribution.
- To compare the TST and IGRA results with the means of numerical continuous variables will be used the Student's t-test for variables with a normal distribution, and the Mann-Whitney test for variables with a non-normal distribution.
- Will be verified the association between the sustainers or non-sustainers status with the categorized variables by the Fisher Exact test. The variables presenting p < 0.05 will be considered a positive association. The variables will be sex, age categorized, duration of illness categorized, alcohol consumption, smoking, presence of other forms of psoriasis associated, blood glucose (normal, diabetic).
- The association between the sustainers or non-sustainers status with the medians/medians of the continuous variables will be verified by t-Student test or Mann-Whitney test, The variables will be the age in years, disease duration in years, BMI, blood glucose in mg/dl, serum levels of INF-γ, TNF-α, interleukin-12, interleukin-17, interleukin-23, ESR, CPR. The association with ESR, CPR, and cytokines will be verified before and after treatment.
- The variables presenting p < 0.05 will be considered a positive association.

.

1. ***Budget****

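### Sustainer status has no fixed horizon: week-12 responders who enter at different dates are all judged in February 2018, and the planned tests ignore the unequal follow-up

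*Protocol*

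**What the plan says.** In the protocol, section 4.2 (Treatment maintenance) defines a sustainer as a patient with a PASI reduction of 50% or more after 12 weeks who "maintained this reduction until the end of the follow-up period". A non-sustainer either never reached 50%, or reached it, lost it during follow-up and needed a change of medication. No duration and no minimum follow-up is given.

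Section 4.1 (Follow up period) schedules PASI every three months and sets one calendar end: "The follow-up period of the study will end in February 2018".

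Section 3.2 has patients included sequentially. Section 3.1 marks "Data collection and follow up" as a single row for 2015 to 2018, starting after ethics approval, and does not separate enrolment from follow-up.

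The Data analysis plan will verify "the association between the sustainers or non-sustainers status with the categorized variables by the Fisher Exact test", and uses the t-test or Mann-Whitney test for continuous variables, including the cytokines. No other analysis of sustainer status is planned.

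**The concern.** Two patients with the same week-12 response can need very different lengths of sustained response to earn the same label. An early entrant has years in which to lose response, a late entrant perhaps months. Being called a sustainer therefore depends partly on entry date.

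Three things are at stake in this secondary objective:

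- The reported sustainer rate cannot be read as a rate at any stated time.
- Responders with short follow-up are labelled sustainers before they have had time to fail, which blurs real differences between the two groups.
- A covariate that drifts with calendar time can look associated with maintenance when it is associated with length of follow-up. The cytokines are a possible case. They are assayed in batch after inclusion ends (section 4.3.2), so early entrants have both the longest storage and the longest follow-up.

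**Working it through.** **The plan's own figure.** The protocol states no figure for the sustainer analysis. Its only calculation is for the paired PASI change ("The sample size calculation was performed considering the effect of MTX on PASI"): "detecting an effect size of 0,65 between pair was necessary 22 pairs", at two-sided 5% and 80% power.
- Normal approximation: ((1.960 + 0.842)/0.65)² = 18.6.
- Adding the small-sample term 1.960²/2 = 1.9 gives 20.5, so 21 pairs.
- Exact noncentral t power is 0.809 with 21 pairs and 0.828 with 22.
- Allowing for a Wilcoxon test, 21/0.955 = 22.0.

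So 22 is reproduced, and nothing below changes it.

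**When inclusion can close.** The assays run only after inclusion ends (sections 4.3.2 and 4.3.3), and laboratory analysis is marked only in 2017 (section 3.1). Inclusion therefore closes in 2017 at the latest and may have closed earlier.

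**Length of follow-up.** Months from entry plus 84 days to 28 February 2018, divided by 3 and rounded down, give the number of quarterly checks after visit two:

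| Entry (illustrative) | Months after week 12 | Checks |
|---|---|---|
| 1 July 2015 | 29.2 | 9 |
| 31 December 2015 | 23.2 | 7 |
| 31 December 2016 | 11.2 | 3 |
| 30 June 2017 | 5.2 | 1 |
| 30 September 2017 | 2.2 | 0 |

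**Chance that a week-12 responder is labelled a sustainer.** The rate of lost response is not in the protocol. I assume h = 5%, 10% or 15% per quarter, constant over time. The chance after k checks is (1 − h)^k:

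| Checks k | h = 5% | h = 10% | h = 15% |
|---|---|---|---|
| 0 | 1.00 | 1.00 | 1.00 |
| 3 | 0.86 | 0.73 | 0.61 |
| 9 | 0.63 | 0.39 | 0.23 |

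**Share of labelled sustainers who would lose response within nine quarters.** If responders are spread evenly over m values of k, the share is 1 − m(1 − h)^9 / Σ(1 − h)^k.
- Checks 3 to 9 (m = 7): 1 − 4.412/5.173 = 0.15; 1 − 2.712/3.803 = 0.29; 1 − 1.621/2.782 = 0.42.
- Checks 0 to 9 (m = 10): 1 − 6.302/8.025 = 0.21; 1 − 3.874/6.513 = 0.405; 1 − 2.316/5.354 = 0.57.
- Checks 7 to 9 only (m = 3), that is, all entry within the second half of 2015: 1 − 1.891/1.992 = 0.05; 1 − 1.162/1.296 = 0.10; 1 − 0.695/0.825 = 0.16.

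**False associations.** This was simulated with 22 patients, 70% week-12 responders (assumed), follow-up uniform over 2 to 35 months (the wide case), and a covariate with no effect on maintenance. An annual loss of 20% or 50% equals 1 − 0.80^(1/4) = 5.4% or 1 − 0.50^(1/4) = 15.9% per quarter, close to the two ends of the range above. Rejection rates of the t-test at a nominal 0.05:

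| Correlation of covariate with follow-up length | 20% annual loss | 50% annual loss |
|---|---|---|
| 0 | 0.050 | 0.051 |
| 0.3 | 0.055 | 0.068 |
| 0.6 | 0.082 | 0.142 |

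Fisher's test on the dichotomised covariate stayed between about 0.02 and 0.06.

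**The case against.** Several stronger readings are tempting, and the protocol does not support them.

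- **That enrolment lasted about three years.** The 2015 to 2018 row covers collection and follow-up together. Entry as late as November 2017 would put visit two in February 2018, after the only year marked for laboratory work. Entry at the end of September 2017 puts visit two in the last days of December. Zero checks is therefore an extreme case, and closure at the end of 2016 or earlier is not excluded.
- **That late entrants are sustainers almost by default.** A patient who misses the 50% reduction at week 12 is a non-sustainer whatever the entry date. The statement fits only late entrants who responded.
- **That the tests will produce spurious findings.** With no link between covariate and entry date the error rate stays at its nominal level. Nothing in the protocol ties sex, smoking or psoriasis form to calendar time, and a storage effect on the cytokines is a possibility, not a documented fact.
- **That the protocol foresees study dropouts and leaves them unclassified.** The words "unless they abandon follow-up" qualify outpatient care continuing after the study period. They do not describe loss before February 2018, and rules for missing data may stand in an analysis plan that is not shown.

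It is also fair to say that this is a secondary objective, and that the comparison of TST and IGRA and the sample size are untouched. All of this limits size and reach. What remains is that the protocol itself fixes both the definition and the tests, and together they do not measure maintenance over one stated period.

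**Conclusion.** The concern holds in a limited form. Sustainer status has no common horizon, and the planned tests ignore how long each responder was watched. With 3 to 9 checks spread evenly and 5% to 15% loss per quarter, about 15% to 42% of labelled sustainers would lose response within nine quarters. The figure is 21% to 57% if checks run from 0 to 9, and 5% to 16% if all entry fell in the second half of 2015. These figures rest on assumed loss rates, a constant hazard and an even spread of entry; the protocol gives none of these.

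The main harm is an undated sustainer rate and diluted associations. Inflated error is a lesser risk, confined to covariates that move with entry date. The point deserves correction but is not critical to the trial.

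**What to change.** In section 4.2 and the Data analysis plan, define sustainer status at one common time after week 12 that every classified patient can reach by February 2018. Choose that time from the closing date of inclusion, and state that date. If inclusion closed at the end of 2016, the third quarterly visit is within reach of all; if it ran to mid-2017, only the first is. Keep week-12 non-responders as non-sustainers and keep the planned tests. Should some patients enter too late for the chosen time, leave them out by entry date alone, responders and non-responders alike.

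Alternatively, among week-12 responders, analyse time from visit two to the first quarterly PASI reduction below 50%, censored at the last PASI visit, with Kaplan-Meier curves and log-rank tests or Cox regression. Report week-12 response separately, since non-responders do not enter that analysis.

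Either route is a change of wording. The quarterly PASI visits are already scheduled, and no further patients or samples are needed. The price is that a common horizon captures fewer losses of response, while the time-to-event analysis will have few events and wide intervals.

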**4.3.2 Cytokines**

Three ml of blood will be collected using a vacutainer-type needle in a tube with citrate anticoagulant. The blood samples will be identified with the inscription "Sample 1" or "SAMPLE 2", date, hour, and research number. Samples will be immediately forwarded to the laboratory.

After 30 minutes of collection, the sample will be centrifuged for 15 minutes at the rate of approximately 1000 × g (or 3000 rpm) at 2-8 degrees. The serum was then separated and frozen between minus 20 ° C and minus 80 ° C. Samples will be stored in separate trays marked with the names “SAMPLE 1”, “SAMPLE 2”. The serum not used in this study will be saved for further research.

Serum levels of the cytokines will be determined quantitatively by the ELISA technique after the end of the inclusion phase. Before starting the ELISA process, calibration tests were performed. Each cytokine will be quantified twice for each sample after the calibration. The sensitivity limit of the methods is equal to 4 pg/ml for IFN-γ, 3.0 pg/ml for TNF-α and IL-23, 2 pg/ml for IL-12 and IL-17.

**4.3.3 QuantiFERON TB Gold In-Tube test**

The QuantiFERON TB Gold In-Tube test (QFT-GIT) (Cellestis, Melbourne, Vic. Australia) will be performed according to the standards described by the manufacturer

1. Collection of material: Blood samples will be obtained before the execution of TT using a vacutainer-type needle in specific collection tubes. One milliliter of blood will be collected from each participant in each tube separately following the sequence: gray-antigen-free tube (null control), red tube-TB antigen (ESAT-6, CPF-10, TB7.7) and purple tube-with hemagglutinin (mitogen or positive control). The tubes will be shared 10 times to contact the blood with the antigens.
2. Sample processing: Samples were incubated within a period of up to 1 hour after collection of blood. The tubes will be gently homogenized by inversion and taken to the oven at 37 ° C and placed vertically for 16 to 24 hours for incubation.
3. After incubation, the tubes will be centrifuged for 15 minutes between 2000 and 3000 RPM for plasma separation. The removed plasma will be placed in cryotubes and then frozen at minus 70 ° for further performance of the second phase of the technique. The cryotubes will be stored with the same identification made on the collection in separately identified trays (SAMPLE 1, SAMPLE 2).
4. The Elisa will be held only after the end of the inclusion period. The exams will be carried out in duplicate.

The regents except the 100X conjugate concentrate will be placed at room temperature for 60 minutes (min). During this time, the standard concentration was 8.0 IU / ml, and the conjugate 100X concentrated, both in distilled water. After reconstitution, the standard will be diluted using the diluent available in the kit: 4 IU / ml, 1UI / ml, 0.25 IU / ml, 0 IU / ml (in the latter, only green diluent).

After the dilutions were performed, 50μL of conjugate will be distributed in each well of the microtiter plate, then 50μL of plasma from the first test step was added to each well. This mixture was stirred for 1 min on a microplate shaker. At the end of this process, the plate containing the samples was covered to avoid exposure to light and incubated for 120 min at room temperature.

**4.3.4 Tuberculin Skin Test**

The tuberculin test will be performed by the intradermal application of 2 UT of purified protein derivative (PPD Rt 23) preferably on the inner surface of the left forearm at the first visit and preferably at the right at the second visit. If there is a psoriasis lesion at the site of application, the arms may be inverted. The results will be read after 72 hours and recorded in millimeters.

#### Data analysis plan

The IBM Statistical Package version 23.0 (IBM corp., Armonk, NY) will be used for the statistical calculations.

- Data will be analyzed descriptively through statistical measures: mean ± standard deviation or median and percentiles for numerical variables and absolute and percentage frequencies for categorical variables.
- It will be verified whether there is a significant change in the results of TST and/or IGRA tests, with 2 or 3 categories, classified according to the variables descriptions by the McNemar test. A P < 0,05 will be considered significant.
- It will be verified whether the difference in the comparison of test results is significant before and/ or after treatment by the McNemar test. A P < 0,05 will be considered significant.
- The agreement between each and between the IGRA and the TST before and after treatment, with two or three categories, will be verified by the Cohen’s kappa.
- For numeric continuous variables, the normality will be tested using the Shapiro-Wilk test. To compare the mean of paired continuous variables will be used the Student's t-test for paired variables for variables with a normal distribution, and the Wilcoxon test for variables with a non-normal distribution.
- To compare the TST and IGRA results with the means of numerical continuous variables will be used the Student's t-test for variables with a normal distribution, and the Mann-Whitney test for variables with a non-normal distribution.
- Will be verified the association between the sustainers or non-sustainers status with the categorized variables by the Fisher Exact test. The variables presenting p < 0.05 will be considered a positive association. The variables will be sex, age categorized, duration of illness categorized, alcohol consumption, smoking, presence of other forms of psoriasis associated, blood glucose (normal, diabetic).
- The association between the sustainers or non-sustainers status with the medians/medians of the continuous variables will be verified by t-Student test or Mann-Whitney test, The variables will be the age in years, disease duration in years, BMI, blood glucose in mg/dl, serum levels of INF-γ, TNF-α, interleukin-12, interleukin-17, interleukin-23, ESR, CPR. The association with ESR, CPR, and cytokines will be verified before and after treatment.
- The variables presenting p < 0.05 will be considered a positive association.

.

1. ***Budget****

| **ESPECIFICAÇÃO** | **EMBALAGEM** | **QNT** | **R$ UN** | **R$ TOTAL** | **ORIGEM** |
| --- | --- | --- | --- | --- | --- |
| **QFT Tubes** | 100 tubes | 1 | 3.099,25 | 3.099,25 | QIAGEN Brasil |
| **QFT 2 Plate Kit ELISA** | 96 tests | 2 | 1984,90 | 3968,00 | QIAGEN Brasil |
| **KIT ELISA IL-12** | 40 tests | 2 | 1.642,00 | 3.284,00 | INVITROGEN |
| **KIT-ELISA IL-23** | 40 tests | 2 | 1.642,00 | 3.284,00 | INVITROGEN |
| **KIT ELISA IL-17** | 40 tests | 2 | 1.642,00 | 3.284,00 | INVITROGEN |
| **KIT ELISA TNF-α** | 40 tests | 2 | 1.642,00 | 3.284,00 | INVITROGEN |
| **KIT ELISA INF-γ** | 40 tests | 2 | 1.642,00 | 3.284,00 | INVITROGEN |
| **Teste Tuberculínico** | 15 tests | 7 | 199,00 | 1.393,00 | Vaccines Rio |
| **Vacuum needle** | 100 Un | 2 | 38,50 | 77,00 | BD |
| **Hemo tube 0.3 ml vacuum collection** | 100 Un | 2 | 68,00 | 136,00 | BD |
| **Vacutainer Vacuum Blood Collection Adapter** | Un | 100 | 0,35 | 70,00 | BD |
| **Total** | | | | **R$ 25,163.25** | |

* The Project will be submitted to the public agencies of the research promotion agencies, as well as sponsorship will be sought from the pharmaceutical industry. The researcher will be responsible for the costs if there is no sponsorship to carry out the research.

1. ***References***

BASSUKAS, I. D.; KOSMIDOU, M.; GAITANIS, G.; TSIOURI, G.; TSIANOS, E. Patients with psoriasis are more likely to be treated for latent tuberculosis infection before biologics than patients with inflammatory bowel disease. Acta Dermato-Venereologica, Estocolmo, v. 91, n. 4, p. 444-6, 2011.

CONSENSO BRASILEIRO DE PSORÍASE 2012 - Guias de avaliação e tratamento Sociedade Brasileira de Dermatologia. – 2 ed. Rio de Janeiro: Sociedade Brasileira de Dermatologia, 2009. 172 p.; 1 ed.; 24 pg.

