#### Study goals and objectives

- 1. **Main objectives**

Verify-in patients with psoriasis, living in an endemic area for tuberculosis and vaccinated with BCG, whether MTX significantly changes the frequency of TST and/or IGRA results and concordance between tests and whether positive tests are associated with age, disease duration in years, blood glucose, body mass index (BMI), PASI (psoriasis area and severity index), CRP, erythrocyte sedimentation rate (ESR), TNF-α, IFN-γ, IL-12, IL17 and IL 23 before and after the use of methotrexate for 12 weeks and PASI reduction after treatment.

- 1. **Specifics objectives**

Determining before and after 12 weeks of methotrexate use in psoriasis patients:

- The value of PASI
- The PASI reduction percentage
- Frequency of QuantiFERON negative, positive, indeterminate, and the test agreement.
- The TST results in mm and the test agreement.
- The agreement between TST and QuantiFERON
- The values ​​and means of the inflammatory tests (ESR and CRP)
- The levels of cytokines; TNF-α, IFN-γ, IL-12, IL17, and IL 23.

Verify if after treatment with methotrexate if there is:

- Statistical difference in frequency of positive/negative/ indeterminates TST
- Statistical difference in frequency of positive/negative/indeterminate IGRA
- Statistical difference in frequency in the agreement between TST and IGRA
- Statistical difference in PASI, cytokines and inflammatory tests levels
- Association between positive and negative tests before and after treatment with sex, age, disease duration, weight, blood glucose, BMI, ESR, CRP, PASI, TNF-α, IFN-γ, IL-12, IL17 and IL 23, absolute PASI and Percentage reduction of PASI before and after treatment.
  1. **Secondary objectives**
- Characterize the clinic and demographic characteristics of the sample following the variables sex, age, weight, BMI, disease duration in years, diabetes, associated psoriasis forms: geographical tongue, palmoplantar psoriasis, psoriasis of the scalp, inverted psoriasis, nail psoriasis, place of residence (urban or rural), contact with cattle, alcohol intake, smoking, prior contact with a tuberculosis carrier, chest X-ray abnormality suggestive of TBLI,

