**Appendix 6- Laboratory Data Record**

| **LABORATORY DATA RECORD** | |
| --- | --- |
| **Initials** | **Research number** |
| **Birthdate** | **Sex** |

| Test | Result Before MTX | Result After MTX |
| --- | --- | --- |
| QuantiFERON TB-Gold |  |  |
| TNF-alfa in pg/ml |  |  |
| INF-Gama in pg/ml |  |  |
| IL17 in pg/ml |  |  |
| IL 12 in pg/ml |  |  |
| IL23 in pg/ml |  |  |
| CRP in mg/dl |  |  |
| ESR in mm/h |  |  |
| Tuberculin skin test |  |  |

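### McNemar on categorised TST and IGRA results in 22 PASI-sized pairs has low power for the main question, and the quantitative readings are not named as outcomes beside it

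*Protocol*

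**What the plan says.** Under Study goals and objectives, the Protocol leads with "whether MTX significantly changes the frequency of TST and/or IGRA results and concordance between tests". The differences to be tested for TST and IGRA are differences in frequency. TST in mm appears only among the quantities to be determined before and after 12 weeks.

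The Data analysis plan names McNemar, at P < 0.05, for a "significant change in the results of TST and/or IGRA tests, with 2 or 3 categories", and Cohen's kappa for agreement. A separate general rule sends paired continuous variables to the paired t-test or the Wilcoxon test. It names neither TST in mm nor QuantiFERON in IU/ml.

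Section 3.2 states: "The sample size calculation was performed considering the effect of MTX on PASI". It continues: "The calculation used the formula for comparing paired differences". The result is 22 pairs for an effect size of 0.65 at 80% power and two-sided 5%. For every other variable it asks only whether the PASI effect would be enough to move it.

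Section 4.2 defines TST and QuantiFERON only as categories. Quantitative readings nevertheless exist. Section 4.3.4 has TST "recorded in millimeters", and section 4.3.3 runs an ELISA against IU/ml standards and classifies from nil, antigen and mitogen values. Appendix 6 has a single line, "QuantiFERON TB-Gold", with one cell per visit and no unit. The cytokine lines on the same form carry pg/ml.

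**The concern.** The study's only power statement concerns PASI, while its lead question is answered by a test that uses only the patients who cross a cut-off. In 22 pairs there may be few of them. A fall in mm or in interferon response that stays on one side of the cut-off contributes nothing.

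The background presents the study as a way to find out whether immunosuppression interferes with screening. A non-significant McNemar result at this size could be taken as reassurance that the data cannot give. The information that would help is already produced by the assays. For QuantiFERON, nothing in the variable definitions or the record form ensures that it is kept.

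**Working it through.** **1. The plan's own figure.** Inputs from section 3.2: d = 0.65, two-sided alpha 0.05, power 0.80.
- Normal formula: (1.960 + 0.842)² / 0.65² = 18.6, so 19 pairs.
- Noncentral t: 21 pairs give power 0.809; 22 pairs give 0.828.
- Wilcoxon adjustment: 21 / 0.955 = 22.0, so 22 pairs.

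The 22 pairs are therefore sound for PASI.

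**2. The smallest result that can be significant.** Exact two-sided McNemar with m changes, all in one direction, gives p = 2 × 0.5^m.
- m = 5: p = 0.0625. m = 6: p = 0.031.
- So at least 6 of 22 patients (27%) must change, and more if any change the other way.
- The uncorrected chi-square, (b − c)²/(b + c), reaches p = 0.046 at 4 against 0.

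**3. McNemar power at 22 pairs, two categories.** The Protocol gives no discordance rates, so they are assumed. Let L be the probability of losing and G of gaining positivity. Sum over m the binomial probability of m discordant pairs (n = 22, probability L + G). Multiply each term by the probability, under Binomial(m, L/(L + G)), of a split with p < 0.05.

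| Lost / gained | Exact | Uncorrected chi-square |
|---|---|---|
| 20% / 5% | 0.12 | 0.28 |
| 25% / 5% | 0.24 | 0.41 |
| 35% / 5% | 0.52 | 0.65 |

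For 80% power the exact test needs about 34% lost with none gained, or about 48% lost against 5% gained. Conversely, 25%/5% would need about 61 pairs and 20%/5% about 92.

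**4. Reading versus category under the same shift.** Assume normal readings with unit variance, correlation r between visits, and baseline positivity B.
- The standardised shift is s (mean difference divided by SD of the difference), so the mean falls by δ = s√(2(1 − r)).
- With cut-off c = Φ⁻¹(1 − B), L = Φ(c + δ) − Φ₂(c, c + δ; r) and G = Φ(c) − Φ₂(c, c + δ; r).
- Example: s = 0.5, r = 0.7, B = 0.5 gives δ = 0.5 × √0.6 = 0.39, L = 0.213, G = 0.062 and exact McNemar power 0.12.

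Ranges over r = 0.5–0.9 and B = 20–50%:

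| Shift s | Paired t on the reading | Exact McNemar |
|---|---|---|
| 0.65 | 0.83 | 0.01–0.34 |
| 0.5 | 0.61 | 0.00–0.20 |
| 0.3 | 0.27 | 0.00 to below 0.08 |

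**5. Non-reactors.** TST in mm was simulated with non-reactors fixed at 0 mm: 40–80% reactors, mean 12 mm, a drop of 2–4 mm, within-person SD 2–3 mm. Wilcoxon power was 0.23–1.00. McNemar power was 0.00–0.08 at the 5 mm cut and 0.00–0.57 at 10 mm. The gain shrinks as more patients read 0 twice.

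**The case against.** **The objective concerns frequencies.** McNemar is the natural test for a change in frequency, and a shift in mm or IU/ml is a different quantity. This stands. It rules out demoting McNemar, but not adding a named analysis beside it.

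**TST in mm may already be covered.** A reader might infer that McNemar is the only test of change in TST. The text does not force that: the specific objectives list TST in mm before and after treatment, and the general paired rule could apply to it. For QuantiFERON there is no such route, because no numeric variable is defined.

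**The quantitative test may not have 80% power.** A reader might carry the 0.65 across to TST and IGRA. Section 3.2 gives it for PASI only and leaves open whether anything else moves, so high power for the reading is an assumption. At a shift of 0.3 it is 0.27.

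**The Protocol does not say exact McNemar.** Correct. The six-patient minimum belongs to the exact test, and the uncorrected chi-square does better, though 0.28 to 0.65 in step 3 is still short of 80%. The calculations also do not describe the three-category version.

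**Other inferences that the documents do not support.** One is a badly inflated error rate from two tests times two categorisations. The two categorisations recode the same reading and are not independent, and exact McNemar at 22 pairs is conservative (null size 0.0005–0.023 for 10–50% discordance). Another is that a repeated tuberculin dose masks an MTX effect; the Protocol says nothing on this. Nor does a blank Appendix 6 cell prove that the IU/ml values will be discarded. It only fails to secure them.

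**Conclusion.** The point holds in a limited form. The lead question rests on McNemar in 22 pairs sized for something else, and power is low for moderate conversion rates. The paired quantitative test had more power than exact McNemar in every scenario tried. How much more depends on a shift that the Protocol does not give: large at 0.5 to 0.65, modest in absolute terms at 0.3, and smaller where many patients read zero at both visits.

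All discordance rates, correlations, baseline positivity values and shifts above are assumptions. Only the reproduction of 22 pairs and the six-patient minimum for the exact test do without them. The gap in naming is clear for QuantiFERON and a matter of reading for TST. The change is worth making before analysis, but it does not invalidate the design.

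**What to change.** - **Data analysis plan:** keep McNemar for the frequency objective and say which version is used. Beside it, name the paired within-patient change in TST (mm) and in TB antigen minus nil (IU/ml), with mitogen minus nil as a further readout. Analyse them by the existing paired t/Wilcoxon rule, with an estimate and 95% CI.
- **Section 4.2 and Appendix 6:** define the QuantiFERON numeric variables and add nil, antigen and mitogen fields in IU/ml for each visit.
- **Section 3.2:** state the conversion rate detectable by McNemar with 22 pairs (exact test, 80% power: about 34% one-way, or about 48% lost against 5% gained). Add that a non-significant McNemar does not show absence of an MTX effect.

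The cost is three record fields and some wording; the ELISA already generates the values. The downside is that a shift in the reading is not a reclassification, so the new analysis complements the frequency comparison and does not replace it.
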